### 3.5. Recruitment and allocation

#### 3.5.1. Nursing students.

Between June 2025 and June 2026, eligible students who agree to participate in the trial will be invited to join a QQ group as part of the volunteer pool. Researchers will create a random grouping table in advance. This table will include study ID numbers, names, and random numbers, along with group assignments. This list will be kept confidential, and access will be restricted to the research team. To ensure random assignment, the RAND function will be used to generate a random number for each individual’s ID. The eligible students will then be divided into three groups (Group 1, Group 2, or Group 3) using a 1:1:1 allocation method. Researchers will assign specific study ID numbers based on the order in which participants join the volunteer pool. They will be informed of their group assignments via QQ one week prior to the intervention. Additionally, students assigned to the implementer role will be further randomly allocated to one of three WeChat groups, each providing detailed implementation plans for different modules.

#### 3.5.2. Middle school students.

Upon reaching the recruitment target, the experiencers will be assigned to three equal-sized teams. Each team will begin at a different module and subsequently rotate through all three modules. The group assignments will be communicated to the head teachers, who will then notify the students.

### 3.6. Study procedure

#### 3.6.1. Development of the student-led healthcare career experience activity for middle school students.

**Development of the student-led healthcare career experience activity.** A preliminary framework for the healthcare career experience activity was established by the project leader and subsequently refined by a guidance team. The project team consisted of eight faculty members, all holding at least a master’s degree and possessing a minimum of five years of teaching experience in nursing education.

**Healthcare career experience activity content design.** For the content design, the Modified Brainstorming Technique was implemented [40]. An inventory of all available nursing positions and educational resources at the institution was compiled. The activities were specifically tailored to the cognitive and physical developmental stages of middle school students, referencing the *Curriculum Guidelines for Comprehensive Practical Activities in Primary and Secondary Schools* (Ministry of Education of the People’s Republic of China, 2017) [41]. Based on peer evaluations, the final content was structured into three experiential modules aligned with key life stages: Early Life, Life in Crisis, and Later Life.

**Healthcare career experience activity process design.** Kolb’s experiential learning theory was applied to create the student-led modules. The process for each station was structured to follow Kolb’s four stages: concrete experience, reflective observation, abstract conceptualization, and active experimentation. A comprehensive description of the activities is provided in Table 1.

**Table 1 pone.0340372.t001:** Comprehensive account of healthcare career experience activities.

Module	Station	Process
Early life experience	1. Childbirth pain & Labor Support	1. Concrete Experience (Observational): Watch the delivery process using VR glasses. 2. Reflective Observation: Share observations and initial feelings about the process. 3. Concrete Experience (Somatic): Experience simulated labor pain with a simulator. 4. Abstract Conceptualization: Summarize the standard nursing interventions for labor support, including breathing coaching and physical comfort measures. 5. Active Experimentation: Role-play as a nurse to provide labor support. Specifically, guide the fellow experiencer through Lamaze breathing rhythms during contractions and perform lower back massage to alleviate simulated pain.
	2. Neonatal care	1.Concrete Experience: Watch implementers demonstrate the correct procedure for bathing and handling a newborn model. 2.Reflective Observation: Share observations on the key safety steps and precautions taken by the implementer. 3.Abstract Conceptualization: Summarize the core principles of neonatal safety, focusing on head support, temperature control, and gentle handling. 4.Active Experimentation: Apply neonatal care principles by performing the standard newborn bathing sequence and executing the correct holding technique to support the head and neck.
Life in Crisis experience	1. CPR(cardio-pulmonary resuscitation)	1.Concrete Experience: Watch implementers demonstrate the full CPR process on a manikin. 2.Reflective Observation: Share observations on key technical actions like chest compression depth and rate. 3.Abstract Conceptualization: Summarize the critical principles of effective CPR, specifically the logic behind the “fast, deep, and consistent” compressions and the 30:2 ratio. 4.Active Experimentation: Execute high-quality chest compressions and ventilation on a manikin strictly adhering to the 30:2 cycle and standard depth requirements.
	2. Heimlich maneuver	1.Concrete Experience: Watch implementers demonstrate the Heimlich maneuver on an adult manikin. 2.Reflective Observation: Share observations on precise hand placement and the direction of force. 3.Abstract Conceptualization: Summarize the principle of creating an artificial cough to expel a foreign object from the airway. 4.Active Experimentation: Perform the abdominal thrust maneuver on the simulation manikin using correct hand positioning to dislodge the foreign body.
Later life experience	1. Geriatric Care & Mobility Support	1.Concrete Experience: Wear a senior-sensation simulator to experience the physical limitations of the elderly. 2.Reflective Observation: Share feelings about the sensory and mobility challenges experienced during the simulation. 3.Abstract Conceptualization: Summarize the nursing principles for fall prevention and mobility assistance for the elderly. 4.Active Experimentation: Act as a community nurse to assist the elderly. Perform a fall risk assessment on a fellow experiencer wearing the simulator and physically assist them to walk safely using a walker.
	2. Rehabilitation Guidance	1.Concrete Experience: Watch implementers demonstrate the use of rehabilitation training instruments. 2.Reflective Observation: Share observations on the specific purpose and target muscle groups of each instrument. 3.Abstract Conceptualization: Summarize the principles of rehabilitation nursing, focusing on promoting fine motor skills and maintaining joint mobility. 4.Active Experimentation: Role-play as a rehabilitation nurse. Instruct the fellow experiencer on the correct operation of the rehabilitation instruments to ensure effective fine motor skill training.

#### 3.6.2. Intervention.

**Intervention Timing Arrangement.** The intervention timing will follow the stepped-wedge design detailed previously (Fig 2). Group 1 (IFF) will initially act as the intervention group (implementers), while Group 2 (OIF) and Group 3 (WOI) will begin in control conditions as Observers and Waitlist, respectively. Subsequently, Group 2 and Group 3 will cross over to the implementer role after the 4th and 8th activity sessions, respectively. After completing four activity sessions, nursing students have the option to continue their participation in a subsequent volunteer pool. The specific roles for each group at each phase are outlined in Fig 2 and Fig 4.

**Fig 4 pone.0340372.g004:**
[figure not shown]
Roles of different groups and details in the healthcare career experience activity.

**Intervention group training.** A training manual for the healthcare career experience activities was developed. The manual includes four sections: activity planning, preparation, detailed implementation steps, and instructor capability assessment. The nursing students will be required to independently study the first two sections using the manual and associated video resources via the Super Star Learning App. The third section, detailing the specific implementation steps for each module, will be taught by the research team members designated for each module. Following this training, all nursing students must pass a practical assessment that simulates the career experience activities before they can act as implementers.

**Intervention implementation.** Each experience module will be led by a designated module leader responsible for organization and quality oversight. At each station, three implementers will be required. One will demonstrate the procedures and explain the materials, while the other two will assist the experiencers with equipment and clarify content. Each implementer will also be responsible for facilitating the reflective stages of the learning cycle with one to two experiencers. To ensure equal opportunities, the roles of the three implementers will be rotated when the next group of experiencers arrives. The experiencers will engage in the activities according to the prescribed segments, as detailed in Table 2. Each station accommodates 3–6 participants per session, with each session lasting approximately 20 minutes in total.

**Table 2 pone.0340372.t002:** The roles of implementers and experiencers in the implementation process.

Step	Module	Content	Location	Time (min)	Action of implementer （nursing students）	Action of experiencer (middle school students)
1	Opening	The aim of activities and announcements	Lecture hall	15	Module leader: Introduction	Assigned to three teams
2	Early life experience	Brief introduction	Medical virtual simulation training center	5	Module leader: Introduction	Listening
2A		Childbirth pain & Labor Support		20	A: Demonstrates the delivery process and labor support skills. B and C: Assist experiencers with equipment and facilitate reflection.	Watch (VR experience) Share (Reflections) Summarize (Support principles) Guide fellow experiencer (Lamaze breathing & Massage)
2B		Neonatal care		20	A: Demonstrates bathing and handling newborns. B and C: The same as the above.	Watch demonstration Share (Reflections) Summarize (Safety principles) Perform bathing and holding
3	Life in Crisis experience	Brief introduction	Emergency training center	5	Module leader: Introduction	Listening
3A		CPR(cardio-pulmonary resuscitation)		20	A: Demonstrates the full CPR process B and C: the same as the above.	Watch demonstration Share (Reflections) Summarize (CPR principles) Perform compressions & ventilation
3B		Heimlich maneuver		20	A: Demonstrates the Heimlich maneuver. B and C: The same as the above.	Watch demonstration Share (Reflections) Summarize (Principles) Practice the Heimlich maneuver
4	Later life experience	Brief introduction	Elderly care training center	5	Module leader: Introduction	Listening
4A		Geriatric Care & Mobility Support		20	A: Demonstrates fall prevention and mobility assistance. B and C: the same as the above.	Watch (Wear simulator) Share (Reflections) Summarize (Nursing principles) Assist fellow experiencer (Walking)
4B		Rehabilitation Guidance		20	A: Demonstrates rehabilitation training instruments. B and C: the same as the above.	Watch demonstration Share (Reflections) Summarize (Rehab principles) Instruct fellow experiencer on using instruments
5	Summary	Sharing the moments during the activities	Lecture hall	15	Module leader: Summary	Watch the video

### 3.7. Data collection and management

Prior to the study, designated researchers will receive standardized training in data collection procedures. Each nursing student will maintain a paper-based growth file, which is anonymized using a unique study ID number. This file contains the self-reported questionnaires collected at each time point, as well as qualitative materials such as feedback from middle school students, academic awards, post-intervention reflections, and a letter written to their future self. These qualitative materials will be used to triangulate and provide context to the quantitative data, partially mitigating potential self-report biases.

Following each data collection point, researchers will check the data for completeness. The nursing students will be asked to supply any missing information immediately to prevent data loss. To ensure confidentiality, all completed growth files will be stored in a locked, secure research data room, with access restricted to the principal researchers. Outcomes will be assessed at baseline (T0) and three subsequent time points (T1, T2, and T3), which correspond to the completion of the 4th, 8th, and 12th activity sessions respectively, as detailed in Table 3.

**Table 3 pone.0340372.t003:** Timeline of measurement details.

Timeline	Group	Status	Demographic characteristics	Professional commitment	Academic Self-efficacy	Learning burnout
T0	Group 1	Implementers	√	√	√	√
	Group 2	Observers	√	√	√	√
	Group 3	Waitlist	√	√	√	√
T1	Group 1	Implementers	–	√	√	√
	Group 2	Observers	–	√	√	√
	Group 3	Waitlist	–	√	√	√
T2	Group 2	Implementers	–	√	√	√
	Group 3	Observers	–	√	√	√
	Group 1	Followup	–	√	√	√
T3	Group 3	Implementers	–	√	√	√
	Group 1	Followup	–	√	√	√
	Group 2	Followup	–	√	√	√

### 3.8. Outcomes and measures

#### 3.8.1. Main outcome: professional commitment.

The primary outcome measure in this study is the change in professional commitment among nursing students. This outcome will be measured using the Undergraduate Professional Commitment Scale, developed by Lian R et al [42]. The scale is organized into four dimensions: emotional commitment, continuing commitment, ideal commitment, and normative commitment. It comprises 27 items, with responses rated on a 5-point Likert scale ranging from 1 (“completely inconsistent”) to 5 (“completely consistent”). Higher scores indicate greater professional commitment. The scale demonstrates strong reliability, with a Cronbach’s α coefficient of 0.927.

#### 3.8.2. Secondary outcome.

**Academic self-efficacy** This outcome will be measured using the Academic Self-efficacy Questionnaire compiled by Liang YS and Zhou ZK [43]. This questionnaire was developed with reference to the academic self-efficacy scale created by Pintrich and DeGroot (1990). It consists of 22 items divided into two dimensions: self-efficacy of learning ability and self-efficacy of learning behavior. The questionnaire has a Cronbach’s α coefficient of 0.89, indicating strong reliability. Responses are collected using a 5-point Likert scale, ranging from 1 (“completely disagree”) to 5 (“strongly agree”), with higher scores reflecting a greater sense of self-efficacy.

**Learning burnout** This outcome will be assessed using the Learning Burnout Scale for college students, developed by Lian Rong in 2005 [44]. This scale includes three dimensions: depression (8 items), improper behavior (6 items), and low sense of achievement (6 items), totaling 20 items. A 5-point Likert scale is used, with responses ranging from 1 (“completely inconsistent”) to 5 (“fully consistent”). The total score ranges from 20 to 100, with higher scores indicating a greater degree of learning burnout. The scale demonstrates strong reliability, with a total Cronbach’s α coefficient of 0.865. The three extracted common factors explain 51.45% of the total variance. In this study, the total Cronbach’s α coefficient for the scale is 0.868.

### 3.9. Statistical analysis

All statistical analyses will be performed using SPSS version 27.0. Demographic variables will be summarized using descriptive statistics. In accordance with the Intention-to-Treat (ITT) principle, all randomized participants will be included in the analysis. Missing data will be handled using the GEE model under the Missing at Random (MAR) assumption. The GEE model will be used to compare differences between and within groups, controlling for time effects and baseline scores of the outcome variables (professional commitment, academic self-efficacy, and learning burnout). To examine the specific impact of each intervention role, the Group variable will be analyzed as a three-level categorical factor (Implementer, Observer, Waitlist). The interaction effect between time and group allocation will also be examined. Post-hoc multiple comparisons between groups will be conducted using the Bonferroni correction. For all analyses, statistical significance is set at a p-value of < 0.05.

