### 3.4. Sample size

The sample size was estimated specifically for a GEE analysis using the longpower package in R statistical software (version 4.4.3). The calculation was designed to detect significant differences in the primary outcome among the three groups across four repeated measurement points. The parameters were set based on standard benchmarks: a significance level (α) of 0.05, a power of 0.80, and a standard medium effect size (δ = 0.50). Regarding the correlation structure, we adopted a conservative estimation. Given that professional commitment is a dynamic construct [36], we assumed a moderate within-subject correlation (ρ = 0.35) [37]. Based on these parameters, the minimum required sample size is 33 participants per group. To account for a potential 10% attrition rate, the final target sample size is set at 110 participants. This method of ensuring adequate statistical power aligns with recommendations in methodological literature [38,39].

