## 5. Limitations

Several limitations of this study protocol should be acknowledged. First, the follow-up period is short. Long-term outcomes, such as career retention after graduation, are not measured. Second, the outcomes rely exclusively on self-reported questionnaires, which may introduce social desirability or recall bias. Third, the study is conducted at a single college. This may limit the generalizability of the findings to other settings. Fourth, the trial is open-label, so blinding is not possible, and the potential for baseline imbalances remains. Finally, the use of a waitlist control group poses a risk. Participants might withdraw or seek other opportunities, which could lead to attrition or self-selection bias.

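### The missing-data sentence credits available-data GEE with validity under MAR that it does not generally have; the likely bias at the planned attrition is small

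*Protocol article*

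**What the plan says.** Section 3.9 gives one sentence on missing data: "Missing data will be handled using the GEE model under the Missing at Random (MAR) assumption". The sentence before it invokes intention to treat and says that "all randomized participants will be included in the analysis". The model is a GEE "controlling for time effects and baseline scores of the outcome variables", with a time-by-group interaction. The article describes no weighting or imputation to go with it.

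Three other places bear on the point:

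- Section 3.4 allows for 10% attrition.
- Section 5 names a risk of the waitlist control: "Participants might withdraw or seek other opportunities, which could lead to attrition or self-selection bias".
- Section 3.3.1 lists students who drop out, are suspended or change major among the exclusions.

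Section 3.7 has students complete missing items at each data collection point, which does not help with students who have already left.

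**The concern.** The sentence treats GEE as if it were itself a method for MAR data. Unweighted GEE solves moment equations on the rows that happen to be observed, and those equations are not generally centred at zero when being observed depends on earlier outcomes. Adjusting for T0 deals with dropout driven by T0, if that adjustment fits. It does not deal with dropout driven by T1 or T2 scores.

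This is an objection to a claim the article makes, not to detail it leaves out. A later analysis plan could add methods, but the sentence would still be wrong. At stake are the between-group contrasts at T2 and T3, and the ITT statement: with T0 on the right-hand side and T1–T3 as outcomes, a student who leaves before T1 contributes nothing.

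**Working it through.** **1. The plan's own figure.** Inputs from 3.4: α = 0.05 (sidedness not stated; two-sided reproduces the result), power 0.80, δ = 0.50, ρ = 0.35, m = 4 measurements.

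n = 2(z₀.₉₇₅ + z₀.₈₀)² [1 + (m − 1)ρ] / (mδ²) = 2(1.960 + 0.842)² (1 + 3 × 0.35) / (4 × 0.25) = 32.18, rounded up to 33.

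This agrees with "the minimum required sample size is 33 participants per group". Then 3 × 33 = 99 and 99 / (1 − 0.10) = 110, also as stated. The present point changes neither figure.

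**2. When available-data GEE is valid.** The equations are Σ XᵢᵀVᵢ⁻¹(Yᵢ − Xᵢβ) = 0 over observed rows.

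- *Missingness depends on group and time only:* covered, because both are in the model.
- *Depends on T0:* covered if the baseline adjustment is correctly specified.
- *Depends on T1 or T2 scores in the same way in all groups:* group contrasts essentially unbiased (within 0.006 SD in the simulation below).
- *Depends on T1 or T2 scores differently by group:* this is MAR and is not generally covered. With near-normal scores, a correct mean model and a working correlation close to the truth, the bias nearly vanishes.
- *Depends on unobserved scores:* not MAR, and not covered by GEE, imputation under MAR or a mixed model.

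**3. Size of the uncovered case.** Large-sample simulation, 300,000 per group, true difference zero, SD 1. The model is group by time plus baseline, fitted to the available T1–T3 data. Dropout before T2 and T3 depends on the last score in Group 3 only (log-odds 1.0 per SD, low scorers leaving), with the same proportion lost in every group. Bias in Group 3 minus Group 1 at T3, in SD:

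| True correlation | Loss by T3 | Independence | Exchangeable |
|---|---|---|---|
| Exchangeable 0.35 | 10% | +0.020 | −0.001 |
| AR(1) 0.7 | 10% | +0.032 | −0.002 |
| Exchangeable 0.35 | 30% | +0.062 | −0.001 |
| AR(1) 0.7 | 30% | +0.079 | −0.024 |

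Separate runs put the loss in Group 3 alone, under an independence working correlation. At 10% loss they gave about 0.03 SD at T3. At about 25% loss, one set gave 0.027–0.054 SD at T3 (log-odds 1.0 and 1.5; exchangeable 0.35 and AR 0.6) and another 0.06–0.09 SD. Together: about 0.02–0.03 SD at 10% and 0.03–0.09 SD at 25%.

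Of these inputs, only the 10% attrition and ρ = 0.35 come from the protocol. The mechanism, slopes, AR structures and higher loss rates are assumptions.

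**4. Set against effect and precision.** Relative to δ = 0.50, the bias is 0.02/0.50 to 0.03/0.50 = 4–6% at 10% loss, and 0.03/0.50 to 0.09/0.50 = 6–18% at 25%. The standard error of a baseline-adjusted contrast at one time point with 33 per group is about √[2(1 − 0.35²)/33] = √(1.755/33) = 0.23 SD. At 10% loss the bias is therefore 0.02/0.23 = 0.09 to 0.03/0.23 = 0.13 of a standard error.

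**5. The ITT statement.** If all of the planned 10% left before T1, 110 × 0.10 = 11 randomised students would have no outcome row. Read literally, 3.3.1 would also exclude them.

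**The case against.** The strongest reply concerns mechanism. Section 5 says only that waitlisted students might withdraw. It does not tie withdrawal to earlier scores, and dropout driven by role alone is covariate-dependent and therefore covered. Table 3 has Group 3 on the waitlist only up to T1, so leaving during that phase precedes any post-baseline score, and T0 is already in the model. In a simulation of exactly that case (independence GEE, dropout on T0), all contrasts were within 0.004 SD of zero with exchangeable ρ = 0.35. With AR(0.6) they reached 0.022 SD at 10% loss and 0.057 SD at 25%, because one common baseline slope does not fit such data. If students leave for outside reasons related to unmeasured outcome, the alternatives offered here are not protected either.

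This stands. A reader might infer from Section 5 that the protocol expects selective withdrawal that will bias the trial; the text does not support that.

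Two further replies stand in part. The bias at 10% loss is small against the standard error. Larger values can be produced (0.07 SD at 10% loss, 0.20 SD at 30%), but they need steep dependence in opposite directions across groups, which nothing in the protocol suggests. And a condensed article need not name a working correlation, so that silence is not a fault. It does mean that the article cannot be read as securing the one condition under which the bias nearly disappears.

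It is also fair that a T0-only student adds little information under any method. That makes the ITT point one of accuracy rather than power.

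**Conclusion.** The point holds as a wrong validity claim with modest consequences. GEE on available rows is not in general an MAR method, and 3.9 offers nothing else. Bias requires dropout that depends on post-baseline scores differently by group, together with a working correlation away from the truth or a misfitting baseline adjustment. The first of these is possible but unstated. On those assumptions, contrasts with Group 3 shift by the amounts given above, in Group 3's favour if its low scorers leave.

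It would go too far to conclude that GEE must be abandoned or that the results would be invalid. The ITT sentence is inaccurate as written for students with T0 only, and it conflicts with 3.3.1.

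**What to change.** Either of two changes makes the MAR statement defensible:

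- Keep GEE, and first multiply impute T1–T3 separately by randomised sequence, using all earlier scores. This preserves the link to the sample-size calculation, which was made for GEE.
- Fit the same mean model as a REML mixed model with unstructured covariance over T0–T3 and T0 in the outcome vector, so that every randomised student with a T0 score enters.

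Reword the missing-data sentence to say which method carries the MAR assumption. Reconcile the exclusion of students who drop out in 3.3.1 with the ITT statement in 3.9, for example by limiting the exclusions to status before randomisation.

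The cost is slightly more analysis work in the software already named, and reliance on an imputation model or on a normal likelihood for a 27-item sum score. Neither option protects against withdrawal that depends on unobserved scores, so a sensitivity analysis for that case would be a sensible addition.

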The core of PAL is that students acquire knowledge and skills through the active support of their peers [22]. The advantage of this model is transforming resource limitations into a teaching opportunity. By allowing students to act as facilitators, this approach greatly reduces the reliance on professional faculty. More importantly, it shifts students from being passive recipients of knowledge to active creators of it. In the process of teaching others, they can develop their leadership, communication, and organizational skills [23–25]. These are key competencies for their future careers that are difficult to achieve in traditional teacher-led models. Moreover, peer interaction can create a more equal learning environment [22]. This may help to increase student motivation and potentially reduce the learning burnout prevalent in nursing programs [26,27]. Previous studies show that student-led activities can effectively enhance professional identity [28–30]. Despite these advantages, the PAL model also faces its own challenges, such as a potential lack of student motivation or conflict within groups, as well as the need for structured training and resource support. All these factors must be considered in the design [31].

Therefore, this study aims to address the following research questions: (1) How was the student-led healthcare career experience activity developed? (2) How will the key outcomes (professional commitment, academic self-efficacy, and learning burnout) change across four measurement time points (T0-T3)? (3) What are the differences in outcomes between Group 1 at T1 and T2? (4) What are the differences in outcomes among all groups at T3?

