## 3. Methods

### 3.1. Study design

This study will utilize an open-label, randomized, stepped-wedge crossover design. Eligible nursing students will be randomly assigned in a 1:1:1 ratio to one of three groups: Group 1 (Implementers+Followup+Followup) (IFF), 2 (Observers+Implementers+Followup) (OIF) or 3 (Waitlist+Observers+Implementers) (WOI). In accordance with the stepped-wedge schedule, all groups will sequentially receive the intervention after transitioning through control conditions (Observer or Waitlist). The specific sequence of roles and intervention timing for each group is detailed in Fig 2. Outcomes will be measured at four time points: baseline (T0), and at three subsequent follow-up points (T1, T2, T3). The schedule of enrollment, interventions, and assessments is shown in Fig 3. This stepped-wedge design was chosen for two main reasons. First, it allows all participants to eventually receive the intervention, which is ethically preferable in educational studies. Second, it helps to control for time-related confounding variables. This protocol is reported in accordance with the recommendations for clinical trials guidelines (SPIRIT) [35].

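### The three-level role factor in the primary GEE has no level for Followup, which is one third of post-baseline cells, and "group" is used for both current role and randomised sequence

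*Protocol article*

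**What the plan says.** Section 3.1 randomises students to three sequences of status: "Group 1 (Implementers+Followup+Followup) (IFF), 2 (Observers+Implementers+Followup) (OIF) or 3 (Waitlist+Observers+Implementers) (WOI"). Measurement is fixed there too: "Outcomes will be measured at four time points: baseline (T0), and at three subsequent follow-up points (T1, T2, T3"). Table 3 in section 3.7 repeats these statuses visit by visit and lists Followup as a status of its own.

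Section 3.9 gives the purpose of the model factor as "To examine the specific impact of each intervention role", and then states that "the Group variable will be analyzed as a three-level categorical factor (Implementer, Observer, Waitlist"). On the analysis set it says that "all randomized participants will be included in the analysis". On the interaction it says: "The interaction effect between time and group allocation will also be examined".

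Two research questions in section 1 involve Followup visits: "What are the differences in outcomes between Group 1 at T1 and T2" and "What are the differences in outcomes among all groups at T3".

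**The concern.** The protocol states the number and names of the factor levels, and they do not match its own schedule. This is a stated rule that conflicts with the design, not a detail left to an analysis plan. An analysis plan that followed the sentence would inherit the conflict.

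The word group also changes meaning within the paragraph. As a role it varies over time within a student. As an allocation it is fixed at randomisation.

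The analyst must therefore decide, without a written rule and in an open-label trial, what to do with Followup visits: leave them out, merge them with Implementer, Observer or Waitlist, or read the labels as names of the arms. These choices do not estimate the same quantity, and the choice affects the primary outcome.

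**Working it through.** **Inputs.** Sequences by visit (section 3.1, Table 3): Group 1 = I, F, F; Group 2 = O, I, F; Group 3 = W, O, I. Within-subject correlation 0.35 and 33 per group (section 3.4). Effects by role are not in the documents, so they are assumed: Waitlist 0, Observer 0, Implementer 0.50 SD, with Followup at 0.50 (sustained), 0.25 (half faded) or 0 (fully faded).

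**The plan's own figure.** The stated 33 per group is reproduced by a two-group, time-averaged comparison over m = 4 measurements, two-sided: n = 2(1.960 + 0.842)² × [1 + 3 × 0.35] / (4 × 0.50²) = 32.18, rounded up to 33. Then 3 × 33 = 99 and 99/0.9 = 110. This formula has no role factor in it, so it does not show how Followup should be coded.

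**Count of cells.** Of 9 post-baseline cells, Implementer has 3, Followup 3, Observer 2 and Waitlist 1. Followup is 3/9, or 3 × 33 = 99 of 9 × 33 = 297 observations. If those are left out, 198 remain. Group 1 keeps one visit of three, Group 2 keeps two, and T3 holds only Implementers, so no roles can be compared at T3.

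**Projection.** The expected coefficients are b = (X′V⁻¹X)⁻¹X′V⁻¹μ, where μ holds the assumed cell means and X has an intercept, two time terms and the role terms (Waitlist reference). V is exchangeable within group. Adjusting for baseline leaves residual variance 1 − 0.35² = 0.8775 and residual correlation 0.35/1.35 = 0.259. Implementer minus Waitlist, true value 0.50:

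| Coding of Followup | Sustained | Half faded | Fully faded |
|---|---|---|---|
| As Waitlist | 0.17 | 0.33 | 0.50 |
| As Implementer | 0.50 | 0.57 | 0.64 |
| Left out | 0.50 | 0.50 | 0.50 |
| Own (fourth) level | 0.50 | 0.50 | 0.50 |

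Coding Followup as Waitlist with a sustained effect also gives a false Observer effect of −0.25. Coding it as Implementer gives a false Observer effect of 0.08 (half faded) or 0.16 (fully faded).

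**Dependence on the working model.** For Followup coded as Implementer, the half-faded and fully faded values are 0.60 and 0.71 without baseline adjustment, and 0.46 and 0.43 under working independence. The direction of the error is therefore not fixed.

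**Labels read as each arm's first role.** The main effect of Group 1 against Group 3, averaged over T1 to T3, is (0.50 + 2f)/3 − 0.50/3, where f is the Followup effect. This is 0.33, 0.17 and 0 for f = 0.50, 0.25 and 0. The same model with an arm-by-time interaction gives 0.50 for Group 1 against Group 3 at T1, whatever f is.

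**Estimability.** Sequence by time fills all 9 of its post-baseline cells. Current role by time with four levels would have 12 cells, of which only 8 occur: Waitlist only at T1, Observer not at T3, Followup not at T1. The four-level main-effects model has 6 parameters and full rank on 9 cells.

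**Limit of the four-level model.** If Followup is 0.25 in the first Followup period and 0 in the second, the Implementer estimate is 0.54 with baseline adjustment (0.56 without). At 0.50 then 0 it is 0.59 (0.62 without).

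**The case against.** The strongest reply is that the three labels simply name the arms by first role. Table 3 supports this: at T0, before any activity, it already labels the groups Implementers, Observers and Waitlist. On that reading group by time is an ordinary three-arm model, it can be fitted, and it gives a randomised Implementer against Waitlist comparison at T1. Research questions 2 to 4, which concern groups at visits, can be answered from it without a Followup level. All of this stands. What it does not meet is the stated aim of isolating each role. After T1 the arm called Waitlist contains Observers and then Implementers, and the arm called Implementer is in Followup.

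Two stronger readings are tempting. A reader might infer that the primary model cannot be fitted at all. The documents do not support that, because the arm-by-time version can be fitted and the role version runs once Followup is left out or recoded. A reader might also infer that the planned interaction is not estimable. The interaction that section 3.9 names is with allocation, and it is estimable; only time by current role is not.

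It is also fair to say that pooling Followup with Implementer as exposed would close the gap if it were stated. It is unbiased when the effect persists in full, but the protocol does not assume this, and research question 3 sets out to examine it. Leaving Followup out gives 0.50 here and every student keeps at least one visit. Still, discarding a third of the post-baseline data sits badly with the intention-to-treat statement.

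**Conclusion.** The point holds as an unresolved conflict between section 3.9 and the design in section 3.1 and Table 3. A stated three-level factor meets a four-status schedule, and one word serves for two variables. Under the assumed effects, the Implementer estimate for a true 0.50 SD ranges from 0.17 to 0.64 across the Waitlist and Implementer codings of Followup with baseline adjustment.

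These values illustrate the dependence and do not predict the result. They rest on assumed role effects, exchangeable correlation of 0.35, equal groups, and the same Implementer effect whether or not a student observed first. The cell count and the missing level rest on no assumption. Nor should a reader infer that a four-level factor is right in every case: it returns 0.50 only if the Followup effect is constant across Followup periods.

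**What to change.** (a) Define current role as a time-varying four-level factor (Waitlist as reference, Observer, Implementer, Followup) following Table 3, with categorical time as a main effect, baseline adjustment, and no interaction between time and current role.

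(b) Define the time by group allocation interaction on the randomised sequence (IFF, OIF, WOI), in a separate model, and use that model for research questions 2 to 4. Use different names for role and sequence throughout section 3.9.

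(c) Add a sensitivity analysis that splits Followup into first period (Group 1 at T2, Group 2 at T3) and second period (Group 1 at T3). This relaxes the constant-effect assumption. In the projection it has 7 parameters at full rank on 9 cells and returns 0.50 in both fading cases above.

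The cost is wording, one extra parameter in the main role model, and some precision. By the same projection with baseline adjustment, the standard error of Implementer minus Waitlist is 0.218 SD, against 0.215 if Followup is pooled with Implementer (0.232 against 0.223 without baseline adjustment).
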